### **5.5.2.Data collection modalities and schedule of withdrawn participants**

Data involving participants having withdrawn their consent will be analyzed only if those participants have responded favourably to this request.

### **5.5.3.Follow-up modalities of withdrawn participants**

A participant's exclusion from the study will bear no consequence on ensuing professional relations regarding this person. In case of any adverse effect, be it serious or not, a precise follow-up will be put in place, in accordance with the gravity and severity of the adverse effect in cause.

## **6. ANALYSIS**

Analysis will concern a number of study questions:

### **6.1. Evaluation of the effect of stress on performance**

At first, we shall estimate the effect of **stress** on team **performance**, using three parts:

- By obtaining evidence of the existence of a biological, electrophysiological and psychological stress, during the progress of various scenarios;
- By estimating the impact of stress on global team performance (determined by degree of respect for the appropriate algorithm);
- By estimating the impact of stress on insertion of an IO access: insertion technique (evaluation scale), decision-making timing and duration;
- By estimating the impact of stress on teamwork: evaluation of leadership (evaluation scale) and communication (evaluation scale).

### **6.2. Evaluation of the effect of repeated simulation sessions**

Next, we shall estimate the effect of **repeated simulation sessions** on a team's **performance evolution** in terms of safety preservation as concerns an infant in a state of shock, using three parts:

- By estimating the impact of repeated simulation sessions on global team performance (determined by degree of respect for the appropriate algorithm);

University Hospital of Poitiers - CHU de Poitiers Sim-Stress

- By estimating the impact of repeated simulation sessions on insertion of an IO access: insertion technique (evaluation scale), decision-making timing and duration;
- By estimating the impact of repeated simulation sessions on teamwork: evaluation of leadership (evaluation scale) and communication (evaluation scale).

Finally, we shall study the effect of the *repeated simulation sessions* on stress by evaluating various stress markers (biological, electrophysiological and psychological), as well as its impact on stress management strategies. We shall so be able to determine if *simulation session repetition*, expected to improve performance, will be accompanied by high stress levels following implementation of stress management strategies, or if it will be accompanied by a decrease in stress levels. Evaluation of the effect of the *repeated simulation session* will be evaluated by comparison of the 2 groups, i.e. the teams that will participate 9 vs. 3 simulation sessions, as described in paragraph 9

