| Expected results                     | Stress decreases team performance, and repeated simulation within a climate of stress allows maintaining high performance levels.                                                                                                                                                                                                                                                                                            |

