##### **9.1.5.Comparison of stress between groups 1 and 2 = Evaluation of the effect of repeated simulation on stress**

The various stress markers (biological, electrophysiological and psychological) will be compared between the 2 groups 1 and 2 by means of a Student's t test or, if necessary, a Mann-Whitney non parametric test.

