##### **9.1.6.Inter-observer reproducibility**

### **9.2. Number of participants to be included in this study and statistical justification**

The necessary number of participants was calculated to answer the main objective of the study: determine if there is relationship between stress and performance.

To determine if there is a relationship between stress and performance, such that the correlation coefficient will attain a value of at least 0,50, with type I error at 5 % and power at approximately 90%, using a bilateral test, the number of subjects to be included is calculated to be 48 (Proc POWER, SIEVE). Our study will include 12 teams of 4 persons each, and each team will include representatives from four status categories (a senior physician, a junior physician (resident ["interne"]), a nurse and an ambulance driver.

To answer secondary objectives, the teams will be distributed in 2 randomised groups, 1 and 2.

It is noteworthy that in a previous study, a sample size of 12 participants each of the professional categories allowed for finding a difference of 2,1 points on an IO access evaluation scale of 20 points (Oriot 2012), knowing that the standard deviation of this score was described to be 1,02 in a previous study.

On the other hand, there is lack of sufficient information in the literature with regard to the number of subjects necessary to determine if there is a difference in the variability of various scores. The power of our study for questions corresponding to secondary objectives will thus be calculated *a posteriori* from the data actually observed.

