### **9.3. Degree of statistical significance**

A *p* score < 0.05 will be considered as statistically significant

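### Section 6.2 promises to determine whether repetition leaves stress high or lowers it, but the only firm stress comparison (9.1.5) cannot support the first answer

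*Protocol*

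**What the plan says.** Section 6.2 opens its statement on stress with "We shall so be able to determine if" and sets out two alternatives: that repetition, from which better performance is anticipated, "will be accompanied by high stress levels following implementation of stress management strategies, or if it will be accompanied by a decrease in stress levels". The effect of repetition "will be evaluated by comparison of the 2 groups, i.e. the teams that will participate 9 vs. 3 simulation sessions", and the reader is sent to section 9 for the method.

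Section 9.1.5 gives the method for stress. The biological, electrophysiological and psychological markers "will be compared between the 2 groups 1 and 2 by means of a Student's t test or, if necessary, a Mann-Whitney non parametric test". Section 9.3 adds only that a p "score < 0.05 will be considered as statistically significant".

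Section 9.1.3 specifies a repeated-measures ANOVA (or Friedman test) across sessions for the performance scores. It then envisages, conditionally, a mixed model that also mentions stress and repeated simulations. Section 9.1.4 compares relative change from T0 between groups, again for performance. Section 9.2 sizes the study for a correlation between stress and performance and leaves power for the secondary questions to be calculated from the observed data.

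**The concern.** The two alternatives in 6.2 are not treated alike. A significant difference in favour of group 1 would support a decrease. Section 9 attaches no positive criterion to the other alternative: no margin, no interval rule and no level at which stress counts as high.

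The contrast is also indirect. Both groups repeat sessions, so 9 v 3 estimates the effect of six further sessions and not a fall from the first session. If stress fell equally in both groups, or stayed high in both, the expected group difference is zero either way.

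Whether better performance comes with persisting or with falling stress is one of the substantive conclusions the protocol promises about repetition. With few teams, a null comparison is likely even if the extra sessions do lower stress.

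**Working it through.** **Plan's own figure.** The plan gives no power or sample size for this comparison, so there is none to reproduce. The 48 in 9.2 is for a correlation of 0.50. By Fisher's z, ((1.960 + 1.282)/0.5493)² + 3 = 37.8, so 38 participants give 90% power and 48 give about 96%. That mismatch is a separate matter and tells us nothing about the group comparison of stress.

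**Inputs from the protocol.** 12 teams are randomised 6 v 6 (4.5.1.2). There are 4 people per team, so 24 v 24 (4.4.2.1). Stress is measured on every participant (7.2). Alpha is 0.05 (9.3). A two-sided test is stated for the main calculation in 9.2 and assumed here for 9.1.5.

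**Assumptions, not in the protocol.** A true difference of 0.5 SD (individual SD) at the session compared; ICC within team from 0 to 0.5; correlation of 0.7 or 0.9 between team means at T0 and at the last session.

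**Participants treated as independent.** SE = √(2/24) = 0.289 SD, so the noncentrality is 0.5/0.289 = 1.73 on 46 df. Power is 39.6% and the miss rate 60.4%. The 95% CI half-width is 2.013 × 0.289 = 0.58 SD.

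**Team means, unadjusted.** SD of a team mean = √((1 + 3·ICC)/4). SE = that SD × √(2/6). Noncentrality = 0.5/SE, on 10 df. Half-width = 2.228 × SE.

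| ICC | SD of team mean | SE | Miss rate | 95% CI half-width |
|---|---|---|---|---|
| 0 | 0.500 | 0.289 | 65% | 0.64 SD |
| 0.1 | 0.570 | 0.329 | 72% | 0.73 SD |
| 0.3 | 0.689 | 0.398 | 79% | 0.89 SD |
| 0.5 | 0.791 | 0.456 | 83% | 1.02 SD |

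Every half-width exceeds 0.5 SD, so an estimate near zero would not exclude a fall of that size.

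**Team means, adjusted for T0.** SE is multiplied by √(1 − r²), on 9 df.

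| ICC | Miss rate, r = 0.7 | Miss rate, r = 0.9 |
|---|---|---|
| 0 | 42% | 6% |
| 0.1 | 52% | 13% |
| 0.3 | 65% | 27% |
| 0.5 | 72% | 39% |

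At ICC 0 the half-width is 2.262 × 0.289 × √(1 − 0.49) = 0.47 SD for r = 0.7, and 2.262 × 0.289 × √(1 − 0.81) = 0.28 SD for r = 0.9.

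**What adjustment does not settle.** Even a precise zero for group 1 minus group 2 leaves the level of stress in both groups undetermined. That needs the change within group 1 as well, and 9.1.5 does not provide it.

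**The case against.** The strongest reply is that the protocol never says a non-significant test will be read as persisting stress. Section 6.2 states an aim and 9.3 defines only significance. That is right. A reader might infer such a rule, but it is not in the text. What stands is that the method 6.2 points to gives the persisting-stress answer no support of its own.

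A reader might also infer that persisting stress could only ever be concluded from a null test. That goes too far. Cortisol, blood pressure, heart rate and STAI are taken the day before, before and after each session and after debriefing (4.4.1), so raised stress could be seen directly. Section 3.2 speaks of variations in stress markers, and the mixed model in 9.1.3 could be turned to stress. But that model is conditional and sits under performance. Section 4.2.2 introduces its relative-variation formula as a study of stress, then applies it to performance scores. None of these is tied to the question in 6.2.

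The unit of analysis is an inference too: 9.1.5 names none, and 6 v 6 follows from randomising teams. The 60% belongs to 24 v 24 independent participants; on team means the range starts at 65%.

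Finally, margins and interval rules for a secondary question are often left to an analysis plan, which may exist. The size of a relevant fall can wait for it. The mismatch between the conclusion promised in 6.2 and the test it cites is in the protocol itself.

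**Conclusion.** The point holds in this form. Under the only stress comparison firmly specified, a non-significant group difference is not evidence that stress persists and cannot tell high in both groups from fallen in both. That follows from the design and holds at any power.

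The size rests on assumptions. For a true 0.5 SD difference, the unadjusted test misses it 60% of the time with participants treated as independent and 65 to 83% on team means (ICC 0 to 0.5). With T0 adjustment on team means the miss rate is 42 to 72% at a baseline correlation of 0.7 and 6 to 39% at 0.9.

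It would be tempting to add that six teams per group could never show stress to be maintained. The figures do not support that: it depends on the baseline correlation, which the protocol does not give.

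**What to change.** - **Section 9.1.5.** Compare the groups on last-session stress in a team-level analysis, or one with a team random effect, adjusted for the T0 value. Report the difference with a 95% CI.
- **Section 9.1.5, added.** Report group 1's own first-to-last-session change in stress with its 95% CI, so that stress that stayed high can be told from stress that fell in both groups.
- **Section 6.2.** State that a non-significant group difference will be reported as not determined, and not as persisting high stress, unless both intervals exclude a fall that the investigators pre-specify as relevant. The size of that fall is theirs to choose and justify before the data are seen.

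The cost is wording and a few intervals from measurements already scheduled at every session; no extra teams or sessions are needed. The downside is that the trial may have to report that the question was not determined.

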## **7. PERFORMANCE AND STRESS EVALUATIONS**

### **7.1. Description of the parameters involved in the evaluation of performance**

Performance will be evaluated using *global team performance*, *IO access insertion* and *teamwork* scales, described in paragraph 4.1

Furthermore, we shall use a double evaluation (direct observation during simulation and indirect observation through viewing of the corresponding video recordings) to analyze the strategies of stress management of the implemented by each senior physician during the simulation sessions.

### **7.2. Description of the parameters involved in the evaluation of stress**

Parameters involved in the *evaluation of stress* will be estimated for every participant, and are described in paragraph 4.2.1

### **7.3. Methods and schedule for collection, quantification and analysis of performance and stress evaluation parameters**

#### **7.3.1. Performance quantification**

Performance quantification will be based upon objective evaluations obtained using a number of evaluation scales (global team performance, IO access, leadership, and teamwork), as conducted by two independent supervisors, direct observers of each simulation session.

Subsequent video recording visualisation by the same two, direct observers, will allow for evaluation of stress management strategies implemented by the team leader.

#### **7.3.2. Quantification of stress**

Quantification of stress will make use of various tools and particular attention:

- Salivary samples for cortisol concentration measurements will be taken one day before the simulation session (at approximately 18H00), the day of the simulation session, just before and right after the simulation session - and preceding as well as following - the debriefing session. Tubes will be preserved in a refrigerator allocated for that purpose in the Simulation Laboratory, and then be sent to the Biochemistry laboratory of the University Hospital of Poitiers (CHU de Poitiers) for analysis ([name] and [name]).
- A Holter device will be placed on each of the male participants by [name], and on each of the female participants by [name], the day before the simulation session (at approximately 18H00). The Holter device will be worn for a total duration of 24 hours. Since the simulation sessions will take place between 14H00 and 15H00 in the Simulation Laboratory, the Holter device will remain in place during 3 hours following the simulation session's end. The recording cassettes will be removed, collected and read once a week in the cardiology department of the University Hospital of Poitiers (CHU de Poitiers) ([name] and [name]).
- A non-invasive measurement of blood pressure will be made the day before the simulation session (at approximately 18H00), the day of the simulation session, just before and right after the simulation session - and preceding, as well as following - the debriefing session. Every measure of blood pressure will be associated to a timely measure of the participant's heart rate.
- Quantification of psychological stress will make use of three questionnaires and SOM score after simulation:
  - SOM: is a score between 0 and 10 obtained by self-assessment after simulation sessions

- STAI is a self-assessment questionnaire, used for estimating both basal and induced, acute stress. Participants will fill out the questionnaire in an isolated room, the day before the simulation session (at approximately 18H00), the day of the simulation session, just before and right after the simulation session - and preceding, as well as following - the debriefing session.
- EIS-R is a self-assessment questionnaire, used for estimating early post-traumatic stress, 7 days following a trauma (in our case, "trauma" corresponds to the simulation session). This questionnaire will be sent out to the participants by e-mail at this time. Answers will be obtained by email return, and collected by a clinical research assistant.
- PCLS is a self-assessment questionnaire, used for estimating late post-traumatic stress, 28 days following a trauma (in our case, "trauma" corresponds to the simulation session). This questionnaire will be sent out to the participants by e-mail at this time. Answers will be obtained by email return, and collected by a clinical research assistant.

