### 3. STUDY OBJECTIVES

#### 3.1. Primary objective

**To seek evidence for the existence of stress**, as it will be assessed by three processes throughout the various scenarios:

- Biological stress (Salivary Cortisol [SC]);
- Electrophysiological stress (Holter 24h, timely measures);
- Psychological stress.

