##### **Biological stress:**

SC will be measured by an Enzyme-Linked Immunosorbent Assay (ELISA) kit (IBL international®, Hamburg, Germany). SC is commonly used to assess stress (Wagner 2010, Beko 2010, Dovio 2010) and this method has been used in simulation (Bong 2010). It will be assessed one day prior to the simulation, just before and right after the simulation session, as well as following debriefing.

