##### 4.4.2.6. Number of salivary cortisol concentration measurements

Salivary cortisol concentrations will be measured the day before the session, then just before and just after simulation, as well as after debriefing that is 4 times per simulation session.

Group 1: 36 cortisol concentration measurements per participant

Group 2: 12 cortisol concentration measurements per participant

Total: 288 x 4 = 1152 cortisol concentration measurements

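### The only cortisol sample from outside the session day is taken 3-4 hours later on the clock than the session samples, so an afternoon fall would bias any comparison with it toward showing stress

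*Protocol*

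**What the plan says.** The primary objective (section 3.1) is "To seek evidence for the existence of stress", by three processes: salivary cortisol, electrophysiological measures and psychological measures. For cortisol, section 4.1 states: "It will be assessed one day prior to the simulation, just before and right after the simulation session, as well as following debriefing". The table in 4.4.1 shows the same four points, and 4.4.2.6 counts them: "Total: 288 x 4 = 1152 cortisol concentration measurements".

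Clock times appear in section 7.3.2. For the day-before sample: "Salivary samples for cortisol concentration measurements will be taken one day before the simulation session (at approximately 18H00". For the session: "Since the simulation sessions will take place between 14H00 and 15H00 in the Simulation Laboratory". The Holter text in that section agrees with these times: "The Holter device will be worn for a total duration of 24 hours", and "the Holter device will remain in place during 3 hours following the simulation session's end".

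No section takes a day-before sample at session time. Section 9 contains no term for time of day. Section 9.1.2 correlates stress markers with performance, and section 9.1.5 compares them between groups 1 and 2. The protocol does not state which comparison of cortisol values is to show that stress exists.

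**The concern.** Cortisol is the first-listed measure of the primary objective. Both randomised groups undergo simulation, so there is no unstressed arm, and the within-person comparison has to supply the reference. Of the four samples, only the day-before one lies away from the session day. That makes it the natural reference, especially as the just-before value may already include anticipation.

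Salivary cortisol generally falls through the day. This is general physiology and the protocol does not state it. The nearest sign is a title in the reference list (section 2.9) about cut-offs specific to midnight, which shows that values are read by clock time but gives no slope between 14H00 and 18H00. If there is a fall over those hours, a reference at 18H00 is lower than an unstressed value at 14H00-15H00 would be. The error then runs in the direction of the hypothesis. A later analysis plan could choose another contrast, but it could not recover an unstressed 14H00-15H00 value that was never collected.

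**Working it through.** **1. Clock times (section 7.3.2).** Holter fitted at about 18H00 and worn 24 h: removed at about 18H00 on the session day. Session ending at 15H00, plus 3 h: 18H00. The protocol's 3 h figure reproduces, so the two clock times are consistent with each other.

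**2. Sample count (section 4.4.2).** (6 × 4 × 9 + 6 × 4 × 3) × 4 = (216 + 72) × 4 = 1152. This reproduces the protocol's total. There is one day-before tube per individual session, 288 in all.

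**3. Clock offset.** 18H00 − 14H00 = 4 h (just before); 18H00 − 15H00 = 3 h (right after). The post-debriefing sample has no stated clock time, so its offset is unknown and it is left out.

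**4. Apparent rise with no stress.** Assume a constant fall of a fraction d per hour. The ratio of the session-time value to the 18H00 value is (1 − d)^(−h), with h = 3 or 4. For example, d = 0.05 and h = 3 give 0.95^(−3) = 1.166.

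**5. Chance of a false rise.** Take a two-sided 5% paired t-test on log cortisol with one pair per participant: n = 48, 47 degrees of freedom, critical value 2.012. The non-centrality is ln(ratio) / (SD/√48). The SD of the log difference is assumed to be 0.5 or 0.8, and pairs are treated as independent. For example, d = 0.05, h = 3 and SD = 0.5 give 0.1539 / (0.5/6.928) = 2.13 and an upper-tail rejection probability of 55%.

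| Assumed fall per hour | Offset | Apparent rise, no stress | False rise, SD 0.5 | False rise, SD 0.8 |
|---|---|---|---|---|
| 3% | 3 h | 9.6% | 24% | 12% |
| 3% | 4 h | 13.0% | 38% | 18% |
| 5% | 3 h | 16.6% | 55% | 26% |
| 5% | 4 h | 22.8% | 80% | 41% |
| 10% | 3 h | 37.2% | 99% | 76% |
| 10% | 4 h | 52.4% | nearly 100% | 95% |

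With no fall, the upper-tail rate is the nominal 2.5%.

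**6. The same-afternoon contrast.** From just before (about 14H00) to right after (about 15H00), the same fall gives an expected change without stress of about −3% to −10%. This works against finding stress.

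**7. After the fix.** With the day-before tube at session clock time, the offset is 0 h, the ratio is 1, and the time-of-day part of the contrast disappears.

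**The case against.** **The biased contrast is not a stated test.** This is correct. No section names the day-before tube as the cortisol reference. The word basal is used for the STAI in 7.3.2 and for the first session in 9.1.2. The paired test above is an illustration, and an analysis plan not shown here may choose another contrast. What remains is that the protocol leaves the day-before comparison open and fixes a sampling time that makes it hard to interpret.

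**The size is assumed.** This is also correct. Neither the hourly fall nor the SD is in the protocol. A range from 12% to nearly 100% shows the direction and that the effect could matter, but not how large it is.

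**A reader might infer that the primary objective cannot fail.** The documents do not support that. The objective also rests on Holter and psychological measures. Cortisol has a same-day pre-simulation sample, and the before-to-after contrast is not inflated. At the mild end of the assumed range, even the biased contrast would usually be non-significant.

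**A reader might also extend the point to blood pressure, heart rate and STAI**, which share the 18H00 time. No direction or size of a time-of-day effect is established for them, so the point stays with cortisol.

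**The group comparison is sound.** Both groups follow the same clock times, so this offset does not bias group 1 against group 2.

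**Conclusion.** The point holds in a limited form. The 3-4 hour mismatch is plain in section 7.3.2, and nothing else in the protocol corrects it. Given an afternoon fall in cortisol, contrasts of the just-before and right-after samples with the day-before sample are biased toward showing stress: by about 10-52% at an assumed 3-10% per hour, with a false-rise rate of about 12% to nearly 100% for n = 48 and an assumed SD of 0.5-0.8. The direction depends only on cortisol falling between session time and 18H00; the size depends on the assumed rate and SD. The randomised comparison and the Holter and psychological measures are not shown to be affected. This is an inexpensive improvement to one primary measure and does not invalidate the primary objective.

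**What to change.** Preferred: in 7.3.2, move the day-before saliva tube to the session clock time, 14H00-15H00. If participants attend only at about 18H00 for the Holter, they can collect that tube themselves and bring it. Sections 2.8 and 5.4 have consent signed the day before the first session, so for that session consent must be obtained before the tube is collected. The number of tubes stays at 1152. The cost is a self-collection or short extra contact before each of up to 288 individual sessions, and self-collected tubes need their collection time recorded.

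Otherwise: state in 4.1 and 9 that the 18H00 cortisol value is descriptive, and base the cortisol evidence for stress on the same-afternoon change from just before to right after simulation. This costs only wording. The text should say that an afternoon fall makes this contrast conservative, and that the pre-simulation value may already include anticipation, so a small or absent rise would not rule out stress.
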